## METHODS

2

The Wake‐Up T2MI Registry is a registry of adults (age ≥ 18 years) who were hospitalized at Wake Forest University Medical Center in a 2‐year period between 1 January 2009 and 31 December 2010, and had T2MI or myocardial injury as defined by the Fourth Universal Definition of MI.^2^ Figure 1 provides an outline of the study design and patient selection.

**Figure 1 clc23182-fig-0001:**
[figure not shown]
Scheme of the Wake‐Up T2MI Registry design

### Data source

2.1

The Clinical and Translational Science Institute (CTSI) at Wake Forest University Baptist Medical Center (WFUBMC), Winston‐Salem, North Carolina, will serve as the data source and primary organization for this registry. WFUBMC is an academic medical center with 885 licensed beds and is designated as a level I trauma center, serving 24 counties in northwest North Carolina and southwest Virginia. Electronic health records from CTSI will be accessed to study demographics, admission diagnosis, discharge diagnosis, laboratory tests, medications, medical history, procedures, and clinical notes for individuals meeting the specified criteria. Mortality data have been obtained from the National Death Index (NDI) and North Carolina State Vital Statistics from 1 January 2009 to 31 December 2017, and will be utilized for ascertainment of death as an outcome. The study protocol has been approved by the regional Internal Review Board at WFUBMC. This registry is registered in Registry of Patient Registries (RoPR) with RoPR ID number of 43530.

### Biomarker

2.2

All troponin samples were analyzed on the Beckman DXI800 (Beckman Instruments, Beckman Coulter, Fullerton, California). This assay has a 99th percentile URL value of 30 ng/L with a coefficient of variation of 10% at 40 ng/L. We used a threshold of 40 ng/L for detection of myocardial injury during the study period.^2^, ^31^

### Identification of study population and patient selection

2.3

Patients with elevated cTnI >40 ng/L from 1 January 2009 to 31 December 2010 were identified using data extracted from CTSI. Due to the absence of International Classification of Disease, Ninth Revision (ICD‐9) code for T2MI and myocardial injury and since administrative coding for T2MI in ICD‐10 were only available in October 2017, ascertainment of T2MI will rely on primary chart review. To limit patients with presumed T1MI, those with ICD‐9 diagnosis of acute MI (410.xx, 411.1) have been excluded from the initial inclusion criteria. The study will exclude patients with pre‐hospital cardiac arrest, patients who were transferred from an outside hospital more than 24 hours after the presentation (to limit selection of patients requiring higher levels of care to minimize the transfer of incomplete or inaccurate information), T1MI diagnosed by discharging physician, traumatic brain injury, readmission, one troponin I level, and significant missing data to sufficiently adjudicate T2MI vs myocardial injury. Data of patients who met the inclusion criteria will be entered into a secure, customized electronic adjudication system for review.

### Ascertainment of clinical data

2.4

#### Presentation

2.4.1

Emergency department notes or admitting physician's notes will be the source of information on the initial presentation of patients (Figure 2). Further information on variables collected during the hospital course, traditional comorbidities and risk factors, baseline medications, laboratory testing variables are provided in Appendix S1.

**Figure 2 clc23182-fig-0002:**
[figure not shown]
Ascertainment of clinical data in the Wake‐Up T2MI Registry

#### Follow‐up

2.4.2

A follow‐up at 180 days, 1 year, 5, and 7 years of all subjects included in the registry will be conducted via a review of the electronic medical records system. At each follow‐up time‐point, health status and any interim cardiovascular (CV) events will be recorded. Vital status will be assessed via the NDI and North Carolina State Vital Statistics including the cause of death.

### Adjudication of T2MI and myocardial injury

2.5

A team of trained study physicians will review all records and utilize the Fourth Universal Definition to classify patients into (a) T2MI, (b) acute myocardial injury, and (c) chronic myocardial injury^2^ (Figure 3). All diagnoses will be adjudicated by two independent adjudicators with disagreements settled by a third adjudicator. All reviewers will have access to all available electronic patient medical records from the index admission described above. To fulfill the biomarker criteria of T2MI, an elevated cTnI of at least >40 ng/L along with an evidence of rise and/or fall of cTnI will be required. If the biomarker criteria is met, clinical conditions with potential to trigger overt ischemia along with any one of the following will be required to be diagnosed as T2MI: (a) symptoms or signs of ischemia recorded in the medical chart; (b) new or presumed new (if unknown baseline) significant ST‐segment/T‐wave changes or new left bundle branch block; (c) development of pathologic Q waves on electrocardiogram; and (d) imaging evidence of new loss of viable myocardium or new regional wall‐motion abnormality.^1^, ^2^ For a diagnosis of acute myocardial injury, an elevated cTnI of at least >40 ng/L along with an evidence of newly detected dynamic rising and/or falling pattern of cTnI and clinical conditions without overt myocardial ischemia will be required. For a diagnosis of chronic myocardial injury, an elevated cTnI of at least >40 ng/L along with stable and unchanging pattern of cTnI and clinical conditions without myocardial ischemia^2^ will be required.

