Our study has the following objectives: (a) to explore clinical characteristics of patients with T2MI and myocardial injury; (b) to investigate the differences in presentation, stratified by age, sex, and race; (c) to characterize utilization of noninvasive and invasive ischemic evaluation strategies in this population; (d) to determine the rates and burden of obstructive CAD; (e) to determine differences in medical and interventional management of T2MI and myocardial injury; (f) to investigate causes of cardiovascular and noncardiovascular mortality in T2MI and myocardial injury; (g) to identify predictors of in‐hospital, 180‐days, 1‐year, 5‐year, and 7‐year outcomes.

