The Wake‐Up T2MI Registry will generate high‐quality clinical data and its longitudinal design will enable follow‐up of short‐ and long‐term outcomes. Results from this registry may be used to structure future risk‐prediction models aimed at T2MI and myocardial injury. Ultimately, results from our registry will provide data on how to delineate better these entities, determine their cardiovascular prognosis, and potentially develop strategies to mitigate their risk. Presently, we have collected data for 2205 of the 2846 planned subjects; careful adjudication will continue to be undertaken to differentiate T2MI, acute myocardial injury, and chronic myocardial injury. Once study participants are adjudicated into gold standard diagnoses, we might better address questions regarding how baseline characteristics as a function of diagnosis, acute management, and prognosis differ.

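### Imaging criterion (d) alone can make a case T2MI, so T2MI-versus-acute-injury comparisons of imaging use or imaging findings are partly circular

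*Protocol article*

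**What the plan says.** **How the label is set.** Section 2.5 of the protocol article (Adjudication of T2MI and myocardial injury) asks for cTnI above 40 ng/L with a rise and/or fall, and a clinical condition able to trigger ischemia, "along with any one of the following will be required to be diagnosed as T2MI". The four alternatives are:
- (a) charted symptoms or signs of ischemia;
- (b) new ST-T changes or new left bundle branch block;
- (c) "development of pathologic Q waves on electrocardiogram";
- (d) "imaging evidence of new loss of viable myocardium or new regional wall‐motion abnormality".

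Acute myocardial injury needs the same dynamic troponin pattern without overt ischemia.

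**What adjudicators see.** Two independent adjudicators classify each case and a third settles disagreements. On access, section 2.5 says: "All reviewers will have access to all available electronic patient medical records from the index admission described above". Section 2.1 (Data source) describes those records: "Electronic health records from CTSI will be accessed to study demographics, admission diagnosis, discharge diagnosis, laboratory tests, medications, medical history, procedures, and clinical notes". No masking is stated.

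**What is then studied.** Objective (c) in the Introduction is "to characterize utilization of noninvasive and invasive ischemic evaluation strategies in this population". Objective (d) concerns obstructive CAD, and objective (e) concerns differences in medical and interventional management of T2MI and injury. The Discussion plans to examine imaging signatures of these disease states. It also says: "Once study participants are adjudicated into gold standard diagnoses, we might better address questions regarding how baseline characteristics as a function of diagnosis", and that sentence goes on to acute management and prognosis.

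**The concern.** Criterion (d) is open only to patients who were imaged. Take two patients with the same troponin pattern, trigger and new wall-motion abnormality, neither of whom meets (a) to (c). The one who was imaged becomes T2MI, and the one who was not stays in acute injury. Having been imaged thus feeds into the label, and a comparison of imaging between labels partly returns the rule that made them.

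Imaging findings are tied to the label more tightly still. Among acute-pattern patients with a trigger, a new wall-motion abnormality on imaging cannot occur in the injury group, because it would have made the case T2MI.

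At stake is whether a reported excess of imaging in T2MI says anything about care. The limitations in section 4.1 cover the single centre, the era, the assay and threshold, and the exclusion of coded T1MI. They do not mention this dependence.

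**Working it through.** The article gives no sample-size calculation, imaging rate or count of cases by criterion, so there is no figure to reproduce. The check is algebraic, with assumed inputs.

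**Inputs (all assumed)**
- t: share of acute-pattern patients who are imaged, unrelated to true class or to (a) to (c). The true odds ratio is therefore 1.
- b: share meeting (a), (b) or (c).
- r: yield of criterion (d), that is, the share of the remaining patients who would show a new abnormality if imaged.

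**Formula**
- P(T2MI | imaged) = b + (1 − b)r
- P(T2MI | not imaged) = b
- Induced odds ratio for imaging, T2MI versus acute injury = [b + (1 − b)r] / [b(1 − r)]

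This exceeds 1 whenever r > 0 and some but not all patients are imaged. It does not depend on t.

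**Results with b = 0.40**

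| r | Calculation | Odds ratio |
|---|---|---|
| 2% | 0.412 / 0.392 | 1.05 |
| 5% | 0.430 / 0.380 | 1.13 |
| 10% | 0.460 / 0.360 | 1.28 |
| 20% | 0.520 / 0.320 | 1.63 |
| 30% | 0.580 / 0.280 | 2.07 |

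With b = 0.20, yields of 2%, 5%, 10% and 20% give 1.10, 1.26, 1.56 and 2.25.

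**As percentages (t = 0.40, b = 0.40, r = 0.20)**
- T2MI share = 0.40 + 0.60 × 0.40 × 0.20 = 0.448
- Imaged in T2MI = (0.160 + 0.048) / 0.448 = 46.4%
- Imaged in injury = 0.192 / 0.552 = 34.8%

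The true rate is 40% in both groups. Cases resting on (d) alone are 0.048 / 0.448 = 10.7% of T2MI.

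**Chance of a false positive.** With t = 0.50, b = 0.20 and r = 5%, imaging appears in 54.5% versus 48.7%. A two-sided 5% test rejects about 73% of the time if all 2846 planned patients had an acute pattern, and about 51% if 60% did. With b = 0.40 instead, the figures are 37% and 24%.

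**What each sensitivity analysis does to imaging use**
- Moving (d)-only cases to injury gives imaging in a share t of both groups, so the odds ratio is 1.00.
- Dropping them gives imaging odds of t/(1 − t) in T2MI and t(1 − r)/(1 − t) in injury. The odds ratio is 1/(1 − r): 1.05 at r = 5% and 1.25 at r = 20%. Exclusion reduces the artefact but does not remove it.

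**The case against.** **The definition is the accepted one.** Criterion (d) belongs to the Fourth Universal Definition, the registry's stated classifier. Full-record review by two adjudicators and a third is a defensible choice for a retrospective registry. This stands, and the criteria are not wrong. But a sound diagnostic rule can still be circular as a grouping variable when the work-up is the result. Double review limits random disagreement, not dependence on a record that all reviewers share.

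**It is easy to read too much into this.** A reader might infer any of the following, which the document does not support:
- *That having a test makes a patient T2MI.* The finding must be positive and new, with a troponin rise or fall and a trigger. Criterion (a) needs no test. Criteria (b) and (c) need an ECG, which matters little if nearly everyone had one; the article does not say.
- *That T2MI will look more catheterised or treated even under identical care.* Angiography, obstructive CAD and treatment are not criteria. Any effect is indirect: unmasked reviewers see them, and imaged patients may go on to more work-up.
- *That every objective is affected.* Objective (c) is worded for the whole population and (d) names no comparison. Only (e), with the Discussion, compares by diagnosis.
- *That long-term mortality is compromised by reviewer knowledge.* Access is confined to the index admission, and deaths come from the National Death Index and state records. Only in-hospital outcomes are visible to adjudicators.

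**The effect may be small.** Yields of 2% to 5% are plausible in patients with no charted symptoms and no qualifying ECG change. They give only 1.05 to 1.13 at b = 0.40. This stands.

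**It may be partly handled already.** Section 2.3 mentions a customized electronic adjudication system, and Figure 3 is not shown. Whether the form records the qualifying criterion is detail an article may omit, so its absence is not counted as an error here.

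**Conclusion.** The concern holds in a limited form. Any T2MI-versus-acute-injury comparison of imaging use or imaging findings is partly circular, because criterion (d) alone can assign T2MI and only to imaged patients. The direction is certain under the stated set-up: the odds ratio for imaging exceeds 1 with no true association. The size is not known. It is about 1.05 to 2.07 for assumed yields of 2% to 30% with 40% meeting (a) to (c), and larger if fewer meet them. These figures assume that imaging is unrelated both to true class and to (a) to (c).

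For angiography, CAD, treatment and in-hospital outcome there is only a possible, unquantified influence through unmasked review or further work-up of imaged patients. Pooled descriptions of work-up and CAD, and the ascertainment of post-discharge deaths, are unaffected.

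**What to change.** 1. Keep the Fourth Universal Definition as the main classifier. A main definition restricted to (a) to (c) would depart from it and would place patients with imaging-proven new abnormalities in the injury group.
2. If the adjudication system does not already do so, record for each case which of (a) to (d) was met.
3. Repeat the by-diagnosis work-up and management comparisons with (d)-only cases moved to acute injury. For imaging use, reclassification is preferable to exclusion, which leaves a residual 1/(1 − r). For management, exclusion or restriction to imaged patients is also informative. Restriction to imaged patients cannot address imaging use itself, nor the finding that defines (d).
4. Do not interpret a T2MI-versus-injury difference in imaging that disappears in that analysis.
5. Add the dependence, and the unmasked review, to the limitations in section 4.1.

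**Cost.** Four tick-boxes, one extra set of tables, and a look-back at any cases already adjudicated without the criterion recorded. Data on 2205 of the 2846 planned patients had been collected by November 2018 and adjudication was continuing, so the look-back grows with delay. Making adjudicators lock the class before opening the angiography, treatment and discharge sections is not needed for this point. It could mean re-review, and a class locked with echo in view would still carry the imaging dependence.

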**Figure 3 clc23182-fig-0003:**
[figure not shown]
Adjudication criteria in the Wake‐Up T2MI Registry

### Study endpoints

2.6

Causes of death will be classified in 1 of 3 categories (1) CV death (secondary to MI, heart failure, sudden cardiac death, stroke, CV procedure, and other CV causes such as pulmonary embolism or peripheral artery disease), (2) non‐CV death, and (3) undetermined cause of death (Appendix S2). Name, social security numbers, and date of birth will be used to match patients with the NDI/North Carolina State Vital Statistics to identified deaths at follow‐up. The definition of CV death will be adapted from the 2014 American College of Cardiology/American Heart Association key data elements and definitions for CV endpoints in clinical trials.^32^ No formal sub‐studies are planned in this study.

### Data management

2.7

All study‐related patient data will be stored on REDCap (Research Electronic Data Capture) tools hosted by Wake Forest CTSI. REDCap is a secure, encrypted, web application for building and managing the online database. REDCap is a Health Insurance Portability and Accountability Act compliant. This web serves as an intuitive interface to enter data with real‐time validation (automated data type and range checks). This platform offers easy data manipulation with audit trails and reports for monitoring and querying of participant records.^33^

### Statistical analysis

2.8

Continuous variables will be reported as means or medians and compared with *t* tests, Wilcoxon rank‐sum, or analysis of variance, as appropriate. Categorical variables will be reported as proportions and frequencies and will be compared with chi‐square or Fisher exact tests. Ordinal variables will be compared with a trend test. Cox proportional hazards modeling will be performed for time‐to‐event analyses. All analysis will be performed on de‐identified data. All analysis was performed using SAS software, version 9.4 (SAS Institute, Inc., Cary, North Carolina).

## RESULTS

3

### Baseline clinical profile of T2MI or myocardial injury

3.1

We plan to collect data from a total of 2846 patients, who met our inclusion criteria over a period of 1 January 2009 to 31 December 2010. As of November 2018, we have collected data for a total of 2205 patients. The baseline characteristics of this initial cohort are detailed in Table 3. The mean age was 65.6 ± 16.9 years, 52.2% were women, and 64% were white. Over two‐thirds (71%) had hypertension, 35% had hyperlipidemia, 30% had diabetes mellitus, and 18.5% had chronic kidney disease at baseline (Table 3). At the time of hospital admission, 40% were on aspirin, 38% were on β‐blockers, 30% were on statins, 29% were on angiotensin‐converting enzyme inhibitors, and 9% were on angiotensin II receptor blockers (Table 3).

**Table 3 clc23182-tbl-0003:** Baseline characteristics of patients in the Wake‐Up T2MI Registry (preliminary data)

Baseline characteristics	Total N = 2205
Age (years), mean (SD)	65.6 (16.9)
Male (%)	1054 (47.8)
Race	
White (%)	1409 (64)
Black (%)	753 (34)
Others (%)	43 (2)

Past medical history	
Hypertension (%)	1576 (71.5)
Diabetes (%)	659 (29.9)
Heart failure (%)	381 (17.3)
Coronary artery disease (%)	313 (14.2)
Previous myocardial infarction (%)	183 (8.3)
Prior percutaneous coronary intervention (%)	27 (1.2)
Prior coronary artery bypass graft surgery (%)	114 (5.2)
Peripheral artery disease (%)	121 (5.5)
Stroke (%)	276 (12.5)
Chronic obstructive pulmonary disease (%)	385 (17.5)
Chronic kidney disease (%)	408 (18.5)
Hyperlipidemia (%)	763 (34.6)
Smoking history (%)	1029 (46.7)
Family history of coronary artery disease (%)	584 (26.5)

Baseline medication use (N = 2205)	N (%)
Aspirin (%)	876 (39.7)
P2Y12 inhibitors (%)	110 (5)
Dual antiplatelet therapy (%)	71 (3.2)
Aspirin or P2Y12 inhibitors (%)	915 (41.5)
Beta‐blocker (%)	838 (38)
Angiotensin‐converting enzyme inhibitor (%)	639 (29)
Angiotensin II receptor blocker (%)	204 (9.3)
Statin (%)	671 (30.4)

*Note*: Continuous variables measured as mean (SD); categorical variables measured by frequency (%).

## DISCUSSION

4

The increasing sensitivity of troponin assays, their wide ranging use, and heightened recognition by clinicians have contributed to an increase in diagnoses of T2MI and myocardial injury. These clinical entities have drawn more attention largely related to challenges in their management and poor short‐ and long‐term outcomes. To date, there have been few randomized clinical trials available to determine the effects of investigational strategies in these cohorts.^34^, ^35^ As such, observational studies defining the epidemiology of these disease entities are of great importance. In the CASABLANCA study^26^ (Catheter Sampled Blood Archive in Cardiovascular Diseases) (ClinicalTrials.gov NCT00842868), a prospective single center cohort examined 1251 patients undergoing coronary and peripheral angiographic procedures, 73.8% had at least one incident of T2MI in median of 40 months follow‐up and found 61% of T2MI had ≥50% coronary obstruction in ≥2 vessels. The role of CAD and mechanism of myocardial injury is being studied in the ongoing, prospective Determining the Mechanism of Myocardial Injury and Role of Coronary Disease in Type 2 Myocardial Infarction (DEMAND‐MI) study (ClinicalTrials.gov NCT03338504). The perioperative period is a unique clinical scenario where patients have high risk of T2MI and myocardial injury. Incidence and Outcome of Perioperative Myocardial Injury After Non‐cardiac Surgery (BASAL‐PMI) study (NCT02573532) is an ongoing observational perioperative study classifying patients into T1MI, T2MI, or myocardial injury using high‐sensitivity cTn assays. Diagnostic strategies to better characterize these entities are urgently needed, as well as targeted therapies to improve outcomes in these patients.

Upon completion of data extraction, the Wake‐Up T2MI Registry will be useful in evaluating use of cardioprotective therapies and their association with long‐term outcomes in this cohort. We would define underlying comorbid disease burden including CAD, peripheral vascular diseases, chronic obstructive pulmonary diseases, obstructive sleep apnea, obesity, hyperlipidemia, and diabetes mellitus. In addition, we would identify important risk predictors of subsequent clinical outcomes, which may help to guide development of strategies to improve outcomes in various subgroups. Furthermore, we plan to evaluate electrocardiographic, imaging, and biomarker signatures of these disease states.

The Wake‐Up T2MI Registry will generate high‐quality clinical data and its longitudinal design will enable follow‐up of short‐ and long‐term outcomes. Results from this registry may be used to structure future risk‐prediction models aimed at T2MI and myocardial injury. Ultimately, results from our registry will provide data on how to delineate better these entities, determine their cardiovascular prognosis, and potentially develop strategies to mitigate their risk. Presently, we have collected data for 2205 of the 2846 planned subjects; careful adjudication will continue to be undertaken to differentiate T2MI, acute myocardial injury, and chronic myocardial injury. Once study participants are adjudicated into gold standard diagnoses, we might better address questions regarding how baseline characteristics as a function of diagnosis, acute management, and prognosis differ.

